### Sample size estimation

2.3

This study is a randomized controlled trial, where the intervention group will receive the mobile health intervention and the standard care group will receive standard care. The outcome measure is the prenatal diagnosis demand. Based on previous randomized controlled trials related to willingness to undergo screening for related diseases, the intervention group’s demand proportion is 53.4%, and the standard care group’s is 34%, showing an increase of approximately 19.4% (28). We predict that the mobile health intervention based on the Behavior Change Wheel theory and Family Health Theory may lead to a doubling of the demand proportion (38.8%), reaching 72.8% (29). The expected demand proportion for the intervention group is 72.8%, and for the standard care group is 34%. Using a two-sided test with α = 0.05, β = 0.2, and power (1-β) = 80%, the sample size ratio between the two groups is 1:1. After using the PASS software (version 2021) to calculate the relevant values, it was determined that 23 participants per group would be required. Considering a 20% dropout rate, the final sample size for each group is 29 participants, for a total of 58 participants.

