### Outcome measures

2.8

There is a total of nine outcomes in the study. Medical staff will use the Questionnaire Star web platform to distribute the questionnaire, and patients will complete the questionnaire online and be instructed by medical staff either in person (at the time of hospitalisation) or by telephone (after discharge). Patient demographic information will be collected through the case system and self-designed questionnaires. (**Table 1**)

**Table 1 T1:** Data collection components and collection timeline.

Type of research	Data collection component	Content	Timepoint	Month 3	After delivery
			Month 0		
Quantitative research	Sociodemographic variables	Sex, age, insurance status, place of residence, average monthly household income, educational level, parents’ education level, area of domicile,	✓		
	Demand for prenatal diagnosis	Willingness for diagnosis, plans for prenatal diagnosis within six months, or having undergone diagnosis	✓	✓	✓
	Pregnancy outcomes	Full-term birth, preterm birth, miscarriage, induced labor due to social factors, and induced labor due to chromosomal abnormalities	✓	✓	✓
	Health Knowledge and Birth Defect Prevention Knowledge Awareness	Self-designed questionnaire	✓	✓	✓
	Obstetric Complications	Gestational hypertension, postpartum hemorrhage, and low-quality infants.	✓	✓	✓
	Depression and anxiety	Patient Health Questionnaire-4 (PHQ-4)	✓	✓	✓
	Decisional Conflict	Decisional Conflict Scale (DCS)	✓	✓	✓
	Self efficacy	Decision Self-Efficacy Scale	✓	✓	✓
	Family Health	Family Health Scale-Short Form (FHS-SF)	✓	✓	✓
	Satisfaction	Decision-making participation satisfaction scale		✓	✓

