### Data analysis

2.9

This study uses IBM SPSS Statistics 24.0 software for quantitative analysis to ensure the accuracy and reliability of the statistical data. In terms of descriptive statistics, we present the baseline characteristics of the participants, with continuous variables being summarized by means and standard deviations or medians and interquartile ranges, while categorical variables are presented as frequencies and percentages. This statistical approach effectively summarizes the basic information of the sample, providing a solid foundation for subsequent analysis. The distribution of continuous data will be tested for normality. Normally distributed data will be presented as mean ± standard deviation (M ± SD), and non-normally distributed data as median (IQR). The Mann–Whitney U test will be used to compare changes in scale scores between baseline and endpoint between the two groups, while the Wilcoxon test will compare differences within each group. The chi-square test will compare the demographic characteristics of the two groups. Statistical significance will be set at p < 0.05, using a two-sided test.

In the case of missing data, assumed to be missing at random, baseline variables will be used as auxiliary variables, and missing data will be imputed using multiple imputation methods. Linear regression and logistic regression will be used for analysis, and the final combined analysis will complete the imputation process.

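### The imputation plan names only baseline variables as auxiliaries and does not admit the Month 3 scores, which are the closest information on missing after-delivery scale scores

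*Protocol article*

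**What the plan says.** Section 2.9 handles missing values in two sentences. It opens with "In the case of missing data, assumed to be missing at random", then states that "baseline variables will be used as auxiliary variables, and missing data will be imputed using multiple imputation methods". It continues: "Linear regression and logistic regression will be used for analysis, and the final combined analysis will complete the imputation process". It gives no predictor list, does not say whether treatment arm enters the imputation model, and does not mention scores from other visits.

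The scale scores are compared as follows: "The Mann–Whitney U test will be used to compare changes in scale scores between baseline and endpoint between the two groups". Which visit counts as the endpoint is not defined.

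Table 1 in section 2.8 ("Data collection components and collection timeline") schedules knowledge, PHQ-4, decisional conflict, decision self-efficacy and family health at Month 0, Month 3 and after delivery. Decision-making satisfaction is scheduled at Month 3 and after delivery, with no Month 0 assessment.

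Section 2.3 plans for losses: "Considering a 20% dropout rate, the final sample size for each group is 29 participants".

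**The concern.** Missing at random is an assumption relative to the variables in the imputation model. If that model holds baseline information alone, the plan assumes that women who leave between Month 3 and delivery resemble those who stay, given their baseline values. If the Month 3 score is included, leaving may also depend on how the woman was doing at Month 3. The second assumption is weaker and the data to support it are already collected.

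Dependence on Month 3 status is plausible here. Section 2.6.1 argues that anxiety and depression affect the women's decisions and behaviour. Only the intervention arm receives counselling and regular contact, so the reasons for leaving may differ between arms.

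Satisfaction is the sharpest case. It has no Month 0 value, so Month 3 is the only earlier measurement on that scale. Imputing it from baseline variables uses no satisfaction information at all.

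What is at stake is the after-delivery comparison of the secondary scale outcomes.

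**Working it through.** **Planned size (not in dispute).** For 72.8% against 34%, two-sided α = 0.05 and 80% power, the unpooled normal formula gives

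n = (1.960 + 0.842)² × (0.728×0.272 + 0.34×0.66) / 0.388² = 22.02, rounded up to 23 per arm.

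With 20% dropout, 23 / 0.8 = 28.75, so 29. This agrees with section 2.3. With all 29 enrolled and 20% lost, 29 × 0.8 = 23.2 women per arm are observed.

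**Assumed inputs, because the protocol gives none.**
- Scores have SD 1, higher is better, and the true effect is 0.5 SD at both visits.
- Correlations are 0.5 (Month 0 with Month 3), 0.4 (Month 0 with after delivery) and 0.6 to 0.8 (Month 3 with after delivery).
- 20% of after-delivery scores are missing, all in women with a Month 3 score.
- The log-odds of being missing rise by the stated slope for each SD worse at Month 3.

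**Bias.** In a large-sample simulation (400,000 records), the after-delivery score is imputed by linear regression and the between-arm difference in mean change is read off. The true value is 0.5.

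| Dropout depends on Month 3 | Corr. Month 3 with after delivery | Arm + Month 0 | Arm + Month 0 + Month 3 |
|---|---|---|---|
| Not at all | 0.6 / 0.8 | 0.50 / 0.50 | 0.50 / 0.50 |
| Both arms, slope 0.5 | 0.6 / 0.8 | 0.49 / 0.49 | 0.50 / 0.50 |
| Both arms, slope 1 | 0.6 / 0.8 | 0.48 / 0.47 | 0.50 / 0.50 |
| Controls only, slope 1 | 0.6 / 0.8 | 0.43 / 0.38 | 0.51 / 0.50 |
| Slope 1 in controls, -1 in intervention | 0.6 / 0.8 | 0.36 / 0.28 | 0.50 / 0.49 |

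A separate run with correlation 0.7 and slopes 0.5 to 1.5 gave 0.46-0.49 for a common mechanism and 0.37-0.45 for dependence in controls only. Taken together:
- Same mechanism in both arms: 0.50 - 0.49 = 0.01 up to 0.50 - 0.46 = 0.04 SD.
- Mechanism differs by arm: 0.50 - 0.45 = 0.05 up to 0.50 - 0.28 = 0.22 SD. The upper end needs the worse-off to leave one arm and the better-off to leave the other. With dependence in controls only, these runs go no further than 0.50 - 0.37 = 0.13 SD.

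With a true effect of zero, a common mechanism gives 0.00, and a mechanism that differs by arm gives -0.08 to -0.21 SD. Swapping the arms reverses the sign, so the error need not be conservative.

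For satisfaction, with no Month 0 score and dependence in controls only (correlation 0.7), the estimate was 0.35-0.43.

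**Precision without informative dropout.** The residual variance given Month 0 is 1 - 0.4² = 0.84. Given Month 0 and Month 3 it is s² = 1 - (0.4² + r² - 2×0.4×r×0.5) / (1 - 0.5²), with r the Month 3 to after-delivery correlation. For r = 0.6, 0.7 and 0.8, s² = 0.627, 0.507 and 0.360. For a baseline-adjusted comparison, the variance per arm is 0.84/23.2 without Month 3 and (0.84 - s²)/29 + s²/23.2 with it. The reduction is 0.2 × (0.84 - s²)/0.84, or 5%, 8% and 11%. For an unadjusted difference in change, (0.4 - 1)²/29 = 0.36/29 is added to both variances, and the reductions become 4%, 6% and 9%.

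**The case against.** A reader might infer that scores are imputed from baseline variables only and that Month 3 is excluded. The text does not say so. Auxiliary variables are normally added to the variables already in the model, and a condensed article may leave the full list to the analysis plan. This stands. What remains is that the article does choose a class of auxiliaries, and that class contains no post-baseline score.

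A reader might also infer that the after-delivery effects are biased in general. They are not. With a common mechanism the bias is zero under the null and at most about 0.04 SD for a 0.5 SD effect. The standard error with 23 women per arm is about √(2 × 0.84 / 23) = 0.27 SD, so that bias is about 15% of one standard error. Material bias mainly needs dropout that depends on Month 3 differently by arm.

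Three further limits stand:
- The 20% dropout has no stated timing. Women lost before Month 3 have no Month 3 score, so it would be wrong to say that one woman in five is affected.
- If the undefined endpoint is Month 3, the main scale comparison is untouched and only after-delivery analyses are concerned.
- Month 3 restores the true value in the simulation because missingness was made to depend on Month 3 alone.

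It may also be tempting to argue that the baseline variables are too many for logistic imputation. That concerns binary outcomes, not scale scores, and nothing says that every baseline variable enters every model.

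**Conclusion.** The point holds in limited form. Section 2.9 names baseline variables as the auxiliaries and does not admit Month 3 scores that the trial collects on the same scales. For women lost between Month 3 and delivery, imputing that way costs precision: 4-11% of the variance if all the planned loss falls in that interval. It can also bias a 0.5 SD effect by about 0.01-0.04 SD with a common dropout mechanism and about 0.05-0.22 SD when the mechanism differs by arm. All these sizes rest on assumed correlations, dropout slopes and timing. The documents do not support saying that Month 3 will certainly be ignored or that the effects will be biased. This is a free improvement to the secondary scale outcomes and leaves the sample size unaffected.

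**What to change.** In section 2.9, add one sentence: the imputation model for after-delivery scale scores includes treatment arm, the Month 0 value of that scale where it exists, and its Month 3 value, in addition to the chosen baseline auxiliaries. For satisfaction this means arm, the Month 3 value and the baseline auxiliaries.

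The sociodemographic variables need not be dropped; the Discussion itself names socio-economic and cultural background as possible influences on outcome. The planned Mann–Whitney comparison need not be replaced. The cost is that sentence, with no new data, visits or participants.

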### Data management

2.10

#### Data collection

2.10.1

All clinical and laboratory data will be carefully recorded in each subject’s medical record and Case Report Form (CRF). The CRF will be the main document for capturing study information, ensuring standardized data organization. The investigator is responsible for verifying the accuracy and completeness of the CRF, cross-checking it with source documents. Each CRF entry will be dated and signed to authenticate the data. A copy of the completed CRF will be submitted to the Principal Investigator (PI), while the original will remain with the investigator. Regular audits will be conducted to ensure data consistency and resolve any discrepancies.

#### Storage and archiving of data

2.10.2

After the trial, all data, including subject IDs, source data, CRFs, and investigator documents, will be securely archived in a designated database, following institutional and regulatory guidelines. The data will be protected from unauthorized access and stored in physical or digital formats, with backups to prevent loss. The data will be retained for a minimum period, in compliance with legal and ethical standards. After the retention period, the data will be securely disposed of, ensuring confidentiality and adherence to data protection laws.

### Clinical supervision

2.11

To ensure trial quality and integrity, clinical supervision will be implemented according to ethical and legal standards, with a focus on ICH-GCP guidelines. Supervision will involve randomized monitoring visits and ongoing oversight, following IZKS Standard Operating Procedures (SOPs). Clinical exams and trial procedures will be observed during in-person visits, with supervisors reviewing the Case Report Forms (CRFs) and cross-checking data against source documents to ensure accuracy. Any discrepancies will be promptly addressed. The investigator will facilitate monitoring by providing access to all necessary study documentation, including CRFs, medical records, and laboratory results, and will support the monitors throughout their visits to ensure efficient data collection. Through strict oversight, the trial will prioritize participant safety, maintain data integrity, and ensure that study objectives are met accurately. Supervisors will offer feedback and corrective actions as needed, helping to identify issues early and ensuring the success of the trial. Regular monitoring and transparent documentation will contribute to the study’s overall validity and reliability.

## Discussion

3

This study aims to assess the impact of mobile health education, grounded in the Behavior Change Wheel theory and Family Health Theory, on the participation rate in prenatal diagnosis and pregnancy outcomes among high-risk pregnant women. To our knowledge, this is the first study to use the Behavior Change Wheel theory and Family Health Theory as the theoretical framework for health management interventions targeting high-risk pregnant women in prenatal screening. High-risk pregnant women are more likely to face pregnancy complications, making improving prenatal diagnosis participation and pregnancy outcomes a key issue in global public health. While some studies suggest that behavioral interventions can effectively improve maternal health behaviors, mobile health education interventions targeting high-risk pregnant women remain limited, especially those combining the of Behavior Change Wheel theory with Family Health Theory.

This study’s innovation lies in integrating its theoretical framework with intervention strategies. The Behavior Change Wheel theory offers a multidimensional framework to help high-risk pregnant women identify and overcome cognitive and emotional barriers to prenatal diagnosis, thereby enhancing their self-efficacy in health behaviors. Family Health Theory highlights the crucial role of family members in managing the health of high-risk pregnant women, with research demonstrating that family support is vital in promoting maternal health behaviors. By integrating these two theories, this study aims to offer a comprehensive support system for high-risk pregnant women, assisting them in understanding and engaging in prenatal diagnosis while also fostering health management during pregnancy.

Another key feature of this study is the use of mobile health education interventions. As mobile health technology advances, personalized intervention methods have emerged as a new trend in public health. Mobile health interventions provide convenient and flexible health management options, particularly for the busy high-risk pregnant population, through real-time health feedback and tailored suggestions. Furthermore, mobile health education is cost-effective and scalable, making it an effective, low-cost intervention for improving prenatal diagnosis participation and pregnancy outcomes among high-risk pregnant women.

This study employs a randomized controlled trial design to assess the effects of personalized mobile health education interventions on prenatal diagnosis participation rates and pregnancy outcomes among high-risk pregnant women. By collecting baseline data from participants, including sociodemographic information and health knowledge, the study aims to deepen our understanding of the factors influencing intervention effectiveness. Based on these data, future intervention strategies could be optimized by tailoring content to better meet the needs of individual participants, thus improving intervention effectiveness and enhancing compliance.

Despite the innovative and practical significance of this study, several limitations require further exploration and resolution in future research. First, the intervention targets only high-risk pregnant women participating in prenatal screening from the Inner Mongolia Maternity and Child Health Care Hospital, with the study sample being limited, which may introduce regional and selection biases. Second, the study primarily relies on self-reported data, which may introduce reporting bias. Additionally, while the study designs an intervention model grounded in the Behavior Change Wheel theory and Family Health Theory, the evaluation of its effectiveness may still be influenced by various factors. For instance, the socio-economic status, cultural background, and family support of the pregnant women may all influence the intervention outcomes. Furthermore, future studies should explore the generalizability of such interventions to low-risk populations, where prenatal diagnosis rates may be constrained by distinct mechanisms.

## Conclusion

4

This study is expected to provide important practical evidence for promoting prenatal diagnosis among the high-risk pregnant women group. If the intervention is effective, this mobile health education model based on the Behavior Change Wheel theory and Family Health Theory will offer medical professionals a new intervention design concept. Furthermore, future research could further expand the intervention content and methods, exploring how emerging technologies (such as big data analysis and artificial intelligence) can be integrated to provide more personalized and precise health guidance for pregnant women.
